### Adverse events

2.9

Adverse events (AEs) are defined as any unfavorable medical occurrence in a study participant receiving the investigational intervention, regardless of its causal relationship to the intervention, in accordance with the National Cancer Institute Common Terminology Criteria for Adverse Events (NCI-CTCAE v5.0) (23).

Given the severity of underlying illness in critically ill patients, abnormalities in laboratory values, signs, or symptoms are common and will not automatically be classified as AEs unless they require clinically significant intervention or are considered clinically relevant at the investigator’s discretion. The underlying condition or diagnosis should be documented whenever possible (e.g., “acute kidney injury” rather than “hyperkalemia”).

AE assessment follows a two-level framework: (1) all-cause AE grading using NCI-CTCAE v5.0; and (2) the following pectin-specific adverse events of interest, which will be actively monitored throughout the intervention period:

a. Abdominal distension: clinical diagnosis based on physical examination and/or intra-abdominal pressure (IAP) ≥ 12 mmHg on routine bladder pressure measurement, corresponding to Grade I intra-abdominal hypertension (IAH) per the World Society of the Abdominal Compartment Syndrome (WSACS) consensus (24).

b. Enteral tube obstruction: inability to aspirate gastric contents or flush the tube with 20 mL warm water, necessitating tube replacement or unplanned cessation of enteral feeding.

c. Ileus: absence of bowel sounds on ≥3 consecutive assessments combined with cessation of stool passage and abdominal distension in the absence of mechanical obstruction, requiring clinical intervention.

d. Intestinal ischemia: radiologically or surgically confirmed bowel ischemia, or strong clinical suspicion based on rising lactate and unexplained hemodynamic deterioration, prompting urgent computed tomography (CT) evaluation. Classified as SAE with mandatory immediate DSMB notification.

e. Aspiration pneumonia: new radiological infiltrates consistent with aspiration pneumonia occurring within 24 h of pectin administration and judged by the investigator as potentially related to altered gastric viscosity.

Causality will be assessed by the site investigator using the WHO five-category classification (Certain/Probable/Possible/Unlikely/Unrelated); events judged Possible or above are included in the safety analysis. A SAE is defined as any event resulting in death, life-threatening condition, prolonged hospitalization, or persistent significant disability. Non-serious AEs will be documented in the eCRF within 24 h of detection. SAEs will be reported to the ethics committee and DSMB in accordance with regulatory requirements.

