### Data and safety monitoring

2.8

An independent Data and Safety Monitoring Board (DSMB), comprising experts in clinical trials, biostatistics, and intensive care medicine, will be established to safeguard participant interests and monitor intervention safety throughout the trial. No formal interim efficacy analyses are planned. This decision was made at the protocol design stage and is consistent with the pragmatic nature of this trial. The DSMB will conduct safety reviews after every 50 participants complete the intervention, focusing on cumulative incidence of pre-specified SAEs, including intestinal ischemia, severe abdominal distension, and aspiration pneumonia and etc. The DSMB may recommend early termination on safety grounds at any time and the TMC will act on such recommendations within 48 h.

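### The intestinal ischemia definition can be met on suspicion that prompts a CT, whatever the CT shows, so refuted cases can enter the incidence the DSMB reviews

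*Protocol article*

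**What the plan says.** Section 2.9 (Adverse events) lists intestinal ischemia as item d among the adverse events of interest specific to pectin. The item has two alternatives. The first is confirmation: "Intestinal ischemia: radiologically or surgically confirmed bowel ischemia". The second follows directly: "or strong clinical suspicion based on rising lactate and unexplained hemodynamic deterioration, prompting urgent computed tomography (CT) evaluation". One consequence applies to both: "Classified as SAE with mandatory immediate DSMB notification".

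Section 2.8 (Data and safety monitoring) sets the timing of DSMB work: "The DSMB will conduct safety reviews after every 50 participants complete the intervention". It describes those reviews as "focusing on cumulative incidence of pre-specified SAEs, including intestinal ischemia, severe abdominal distension, and aspiration pneumonia and etc". The board may recommend early termination on safety grounds at any time, and the TMC is to act within 48 h. No numerical stopping threshold is given.

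Three other statements bear on the point:

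- Section 2.9 asks that the underlying condition or diagnosis be documented where possible.
- It defines seriousness by outcome: "A SAE is defined as any event resulting in death, life-threatening condition, prolonged hospitalization, or persistent significant disability".
- It applies a causality filter: "events judged Possible or above are included in the safety analysis".

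Section 2.2 says that blinding treating clinicians was not feasible.

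**The concern.** A case definition used for an incidence count should separate patients who had the event from those in whom it was looked for and not found. Here the second route is complete once suspicion has led to a CT request. A scan showing normal bowel does not undo it, so confirmed, unresolved and refuted cases fall under one label.

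Two things follow. First, a rare and serious harm may be counted together with a diagnostic work-up, which dilutes a true difference even if suspicion is equally common in both arms. Second, suspicion is a judgement by clinicians who may know the allocation, and the protocol names the event as one of interest for pectin. If the threshold for suspecting ischemia is lower in pectin patients, the count could differ between arms without any difference in bowel ischemia. Either way, the board would be weighing a figure that does not measure what its name says.

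**Working it through.** **No protocol figure to reproduce.** The documents give no ischemia rate, no rate of negative CTs and no stopping threshold. The check is therefore a reading of the text, followed by an illustration on assumed rates.

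**Reading, step by step (protocol article).**

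1. Section 2.9, item d: two alternatives joined by *or*. The second needs strong suspicion, rising lactate, unexplained hemodynamic deterioration and a prompted CT. It sets no condition on the result.
2. Same item: the SAE classification and the immediate DSMB notification apply to the item as a whole.
3. Section 2.8: the DSMB reviews cumulative incidence of pre-specified SAEs, and intestinal ischemia is the first one named.
4. Is a refuted case removed anywhere? There are three candidates in section 2.9:
   - The instruction to document the underlying diagnosis could lead a site to record another cause. It is general and does not say that an event already classified under item d is withdrawn.
   - The causality filter tests relation to the intervention, not whether ischemia was present. The text does not say that it governs the DSMB counts.
   - The outcome-based SAE definition would not by itself cover a refuted suspicion, but item d assigns SAE status directly.
5. So, as written, a CT-negative patient qualifies, and no stated rule takes that patient out on diagnostic grounds.

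**Illustration (all rates assumed).** Let t be the true ischemia rate and f the rate of CT-negative suspicion, with every true case confirmed. The arm size of 106 is from section 2.6.

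- Share of counted cases that are true = t / (t + f)
- Expected counted cases = 106 × (t + f)
- Expected confirmed cases = 106 × t
- Chance of 2 or more cases among 25 pectin patients at the first review (50 patients assumed to split evenly) = 1 − (1 − p)^25 − 25p(1 − p)^24, with p = t + f for counted cases and p = t for confirmed cases

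| t | f | True share | Counted of 106 | Confirmed of 106 | P(2 or more counted of 25) | P(2 or more confirmed of 25) |
|---|---|---|---|---|---|---|
| 0.5% | 1% | 33% | 1.59 | 0.53 | 5.4% | 0.7% |
| 0.5% | 5% | 9% | 5.83 | 0.53 | 40.3% | 0.7% |
| 1% | 1% | 50% | 2.12 | 1.06 | 8.9% | 2.6% |
| 1% | 5% | 17% | 6.36 | 1.06 | 44.7% | 2.6% |
| 2% | 1% | 67% | 3.18 | 2.12 | 17.2% | 8.9% |
| 2% | 5% | 29% | 7.42 | 2.12 | 53.0% | 8.9% |

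**Unequal suspicion (assumed).** Take t = 1% in both arms, with f = 5% on pectin and 2% on control:

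- Pectin: 106 × (0.01 + 0.05) = 6.4
- Control: 106 × (0.01 + 0.02) = 3.2

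The ratio is 2 although the true rates are equal. It comes entirely from the choice of 5% against 2%. Rounded to 6 and 3 of 106, Fisher's exact test gives p = 0.50.

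**The case against.** The strongest reply has four parts.

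- **Follow-up rules may sit elsewhere.** How a suspected event is followed up and tabulated is often set in a full protocol or DSMB charter, and neither is shown. This stands as a limit: such a document could adjudicate refuted cases. But the article does state the case definition, and the definition itself admits them.
- **The board need not act on a raw count.** It is independent, includes intensive care and biostatistics experts, hears of each case at once and has no numerical threshold. This stands. A reader might infer that negative scans could trigger termination; the documents do not support that. The board recommends, the TMC acts, and nothing suggests that the CT result would be withheld.
- **The route is narrower than any lactate rise.** It requires strong suspicion and unexplained deterioration together. This stands. It would go too far to say that the count mainly measures how often a CT is ordered, because no passage gives the frequency of this combination.
- **An inclusive definition is a defensible, cautious choice for a rare harm.** This holds for notification, which should stay as it is. It is weaker for an incidence count, where the cases can be separated at almost no cost.

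Two further limits apply. The Discussion says that physicians responsible for nutritional therapy were blinded. This sits badly with section 2.2 and does not clearly cover whoever requests the CT, so differential suspicion is possible but not shown. Section 2.7 defines the safety population by receipt of the study intervention, so it is uncertain whether a two-arm comparison of this event would be made as illustrated.

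**Conclusion.** The point holds in a limited form. Under the stated definition, a patient with a negative CT meets the criteria for intestinal ischemia and can enter the cumulative incidence of pre-specified SAEs. The safeguards in section 2.9 may remove some of these patients, but none asks whether ischemia was present.

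A reader might infer that every refuted case stays classified as ischemia, or that a false two-fold pectin signal is to be expected. The documents support neither. They do not say that such cases are kept, only that no rule removes them. The doubling rests wholly on assumed rates and would not be persuasive evidence even if it occurred.

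The size of any distortion is unknown. Over the assumed ranges, true cases would be 9% to 67% of those counted, and the chance of two or more counted cases among 25 pectin patients would be 5% to 53%, against 0.7% to 9% for confirmed cases. This rests on complete confirmation of true cases and an even split at the first review. The primary outcome is not touched. The change is worth making but moderate in weight.

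**What to change.** Leave the trigger and the immediate DSMB notification on suspicion unchanged. Add one eCRF field for the CT or surgical result. In the DSMB reports and the trial results, show three separate rows by arm:

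1. confirmed ischemia;
2. suspected, not confirmable (for example, the patient could not be imaged);
3. suspected, refuted.

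Use rows 1 and 2 together as the headline rate and print the all-suspected total beside it.

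The cost is a wording change and one data field, for the result of a scan that the definition already presupposes. It adds no procedure and delays no alert. The one downside is that a false-negative CT drops out of the headline rate. That case stays visible in the all-suspected total, which is why refuted cases should be shown and not discarded.

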## Discussion

3

Enteral nutrition is the preferred route of medical nutrition therapy for critically ill patients (25). However, enteral feeding intolerance remains a frequent challenge in daily clinical practice (4, 26). Feeding intolerance often results in suboptimal nutrient delivery and gastrointestinal (GI) disturbances, and has been associated with prolonged mechanical ventilation, extended ICU and hospital length of stay, and increased mortality (4, 27).

To improve GI tolerance in critically ill patients, enteral formulas supplemented with dietary fiber have been developed and increasingly used (28). Current guidelines provide inconsistent recommendations regarding fiber supplementation in the ICU setting. The ASPEN guideline suggests considering the routine use of fermentable soluble dietary fiber in stable medical and surgical ICU patients (1), whereas the ESPEN guideline does not specifically address dietary fiber use in critical illness (2). A recent systematic review and meta-analysis including 20 RCTs demonstrated very low-certainty evidence suggesting potential clinical benefits of fiber-supplemented EN (29). Furthermore, trial sequential analysis indicated that the cumulative information size remains insufficient, highlighting the need for additional well-designed trials to clarify its efficacy.

Pectin, a fermentable soluble dietary fiber, has been proposed as a promising option to improve feeding tolerance and control diarrhea in critically ill patients. Several biological mechanisms may underlie these effects. Upon exposure to gastric acid, pectin undergoes gel formation, which may slow gastric emptying and prevent rapid intestinal transit (14). In the colon, the water-soluble fibers of pectin exhibit high water-binding capacity, potentially increasing stool consistency and attenuating excessive propulsive colonic contractions (30). In addition, pectin is fermented by colonic microbiota into short-chain fatty acids (SCFAs) (31), which serve as the primary energy source for colonocytes. SCFAs promote mucosal repair and enhance intestinal barrier integrity, thereby reducing bacterial translocation and potentially improving GI function and feeding tolerance (32, 33). Last, pectin may form a protective physiological barrier along the intestinal epithelium, limiting pathogen adherence and contributing to the maintenance of intestinal microbial homeostasis (34).

Diarrhea represents one of the most common manifestations of EN intolerance in the critically ill, with reported rates of 10%–70% among ICU patients receiving EN, reflecting genuine variability across populations, feeding routes, and definitions (9, 15). Given the multiple mechanisms by which pectin may attenuate diarrhea, including increased stool consistency, modulation of colonic transit, and enhancement of intestinal barrier integrity, diarrhea incidence is therefore included as a pre-specified secondary outcome to provide exploratory evidence on pectin’s antidiarrheal effects in this population.

Several limitations should be acknowledged. First, no placebo was provided to patients assigned to the control group, which may introduce performance bias. A matched placebo was not feasible, as low-esterified pectin rapidly forms a visible and palpable gel via Ca^2+^-mediated crosslinking when mixed with enteral formula, and no biologically inert alternative can currently replicate this transformation. To address this potential bias, treating physicians responsible for nutritional therapy were independent of the study investigators and remained blinded to treatment allocation. Furthermore, both groups were managed under the same standardized CCCNTG feeding protocol to ensure uniform nutritional management, and all outcome assessments and statistical analyses were conducted by personnel blinded to treatment allocation.

Second, the control group receives usual nutritional care without a mandated fiber-free formula, which may introduce confounding if fiber-containing formulas are used. Given the limited use of fermentable soluble fiber in standard ICU enteral formulas across participating centers, the magnitude of this confounding effect is expected to be modest.

Third, the viscosity-enhancing properties of low-esterified pectin may compromise the reliability of gastric residual volume (GRV) measurement in the intervention group, as the viscoelastic gel formed in the gastric lumen can resist aspiration through a nasogastric tube, leading to systematic underestimation of true residual content. As our protocol does not mandate GRV-based EN management, consistent with current evidence and guideline recommendations, EN tolerance is assessed using functional clinical endpoints. The relationship between pectin-induced viscosity and gastric emptying in critically ill patients warrants further investigation.

Fourth, given the 7-day intervention period, the trial is not powered to detect differences in longer-term clinical outcomes; secondary outcomes should therefore be interpreted as exploratory and hypothesis-generating.

In summary, this multicenter RCT aims to address an important gap in the current evidence regarding dietary fiber supplementation in critically ill patients. By rigorously evaluating the effects of low-esterified pectin on feeding tolerance and EN delivery, the findings have the potential to advance our understanding of the role of dietary fiber in EN for critically ill adults and inform the design of future confirmatory trials.

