### Randomization and blinding

2.2

The randomization sequence will be generated by an independent statistician using SAS Version 9.4 with a fixed block size of 4, ensuring allocation in a 1:1 ratio. Randomization will be stratified by study site. Allocation concealment will be ensured through a secure, encrypted, password-protected central web-based randomization system.^1^

Blinding of participants and treating clinicians was not feasible because pectin supplementation changes the handling and administration characteristics of the enteral formula, making it distinguishable from standard care during routine clinical practice. No placebo will be provided to the control group. Nonetheless, outcome assessors and data analysts will remain blinded to group assignments to minimize assessment and analytic bias.

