#### Intervention group

2.3.1

The intervention will consist of administering pectin-supplemented EN from randomization until the earliest of the following events: (1) discontinuation of gastric feeding, either due to successful transition to full oral intake or intolerance requiring a switch to post-pyloric feeding or PN; (2) ICU discharge; (3) death; or (4) 7 days after enrollment.

The pectin supplement (Yaoshun^®^ citrus pectin, Qirui medicine, China) consists of low-esterified citrus pectin with a degree of esterification of 5%–15% and is formulated to maintain relatively low viscosity during tube administration. In the presence of calcium ions contained in the enteral formula, the pectin can undergo calcium-mediated gelation, forming a semi-solid gel and increasing intragastric viscosity, which may help reduce retrograde flow and gastroesophageal reflux. The supplement will be administered at a total daily dose of 90 g per 500 mL of enteral formula, delivered as divided 45 g boluses via gastric tube. One bolus will be administered immediately before initiation of EN, with subsequent boluses given after every 250 mL of formula infusion. To minimize the risk of tube occlusion, the feeding tube will be flushed with 20 mL of warm water before and after each pectin administration.

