#### ICU procedures common to both arms

2.3.3

Once randomized, the treating clinical team will determine the target infusion rate (mL/hour) for continuous EN to meet the energy requirement. Selection of the EN formula, estimation of protein needs, and blood glucose management will follow the CCCNTG feeding protocol or the standard procedures of each participating site.

Feeding intolerance will be managed according to the CCCNTG feeding protocol. Initial strategies include the use of prokinetic agents (e.g., erythromycin, metoclopramide) and adjustments to the EN formula. For patients with persistent gastric intolerance despite prokinetic therapy, postpyloric feeding will be implemented. If intolerance continues even after postpyloric feeding is attempted, PN will be commenced.

All patients will receive routine clinical care as determined by the local ICU team, including monitoring of vital signs, analgesia and sedation, fluid therapy, mechanical ventilation, renal replacement therapy, and vasoactive support. All cointerventions will be undertaken at the discretion of the treating clinicians and documented in the medical record.

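### The Discussion claims the treating nutrition physicians were blinded, while section 2.2 says treating clinicians could not be

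*Protocol article*

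**What the plan says.** Section 2.1 calls the trial open-label. Section 2.2 (Randomization and blinding) gives the reason: "Blinding of participants and treating clinicians was not feasible because pectin supplementation changes the handling and administration characteristics of the enteral formula". It adds that the control group gets no placebo, and it limits blinding to two groups: "outcome assessors and data analysts will remain blinded to group assignments".

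The limitations part of the Discussion accepts that the lack of a placebo may cause performance bias and explains why none could be made: "low-esterified pectin rapidly forms a visible and palpable gel". The next sentence offers a mitigation: "To address this potential bias, treating physicians responsible for nutritional therapy were independent of the study investigators and remained blinded to treatment allocation". Two more follow: a feeding protocol shared by both arms, and blinded outcome assessment and analysis.

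On who controls feeding, section 2.3.3 says that after randomization "the treating clinical team will determine the target infusion rate (mL/hour) for continuous EN", and later: "All cointerventions will be undertaken at the discretion of the treating clinicians". Section 2.3.1 gives pectin as a bolus before feeding starts, "with subsequent boluses given after every 250 mL of formula infusion", with a tube flush before and after each dose. It ends pectin on, among other events, "intolerance requiring a switch to post-pyloric feeding or PN".

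**The concern.** A physician who treats the patient and directs nutrition is a treating clinician. Section 2.2 says such people could not be blinded; the Discussion says they were. Both are current text. A fuller protocol or an analysis plan would not resolve this, because the article states both versions rather than leaving one out.

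The conflict falls on the people whose decisions feed the primary outcome. Section 2.4.1 defines that outcome as Day 5 EN energy divided by a target. The 25 kcal/kg formula fixes the target, so influence runs through the numerator: whether feed is held, for how long, and when the patient moves to post-pyloric feeding or PN. Blinding the assessors and analysts protects how delivered energy is recorded and compared. It does not protect how much is delivered.

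If section 2.2 is right, the Discussion credits the trial with a safeguard it does not have. If the Discussion is right, section 2.2 misreports who was blinded. Either way, a reader judging risk of bias cannot tell how far a difference in EN delivery reflects tolerance and how far it reflects knowledge of the arm.

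**Working it through.** **1. The statements side by side.**

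| Question | Section 2.2 | Discussion |
|---|---|---|
| Treating clinicians | Blinding not feasible | Those responsible for nutrition remained blinded |
| Outcome assessors | Blinded | Blinded |
| Analysts | Blinded | Blinded |

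Only the first row conflicts.

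**2. Can both be true?** Only if the nutrition physicians were a separate group, kept apart from pectin handling. Checked against the rest of the article:

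- Section 2.3.3 gives the target rate to the treating clinical team and names no separate prescriber.
- Section 2.3.1 ties pectin to feed volume. At an assumed 1500 mL/day, 1500/250 = 6 pectin boluses fall on a continuing day, in one arm only.
- Section 2.3.1 also stops pectin when intolerance forces a change of route, so a decision in the nutrition physician's remit ends the study product.
- The Discussion itself says the gel can be seen and felt.
- Nothing says how pectin orders, boluses or gel would be hidden from a prescriber.

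The reconciling reading is possible but undescribed. Even if it is true, section 2.2 needs correcting, since it lists only assessors and analysts as blinded.

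**3. The plan's own figure.** Inputs from section 2.6: control mean 62.9%, SD 31.1%, relative increase 20%, power 80%, two-sided alpha 0.05.

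- Design effect: 0.20 × 62.9 = 12.58 points.
- n per arm = 2 × (1.960 + 0.842)² × 31.1² / 12.58² = 95.9, so 96. This matches the plan.
- SE of the difference at 96 per arm: 31.1 × √(2/96) = 4.49 points.

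**4. Scale, on an assumption.** The article gives no figure for a difference between arms in discretionary holding of feed. I take 0 to 1 h/day as an assumption, in either direction. An hour can be costed in two ways:

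- at the full target rate with no catch-up: 100/24 = 4.17 points;
- at the mean delivery in section 2.6: 62.9/24 = 2.62 points.

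For a shift b, rejection under no effect = P(Z > 1.96 − b/SE) + P(Z < −1.96 − b/SE). If the shift works against pectin, power = P(Z > 1.96 − (12.58 − b)/SE).

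| Difference in holding | b (points) | Rejection under no effect | Power if against pectin |
|---|---|---|---|
| 0 | 0 | 5.0% | 80% |
| 0.5 h, mean rate | 1.31 | 6.0% | 71% |
| 0.5 h, full rate | 2.08 | 7.5% | 65% |
| 1 h, mean rate | 2.62 | 9.0% | 60% |
| 1 h, full rate | 4.17 | 15.3% | 47% |

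The table shows only how sensitive the outcome is to feeding decisions. It does not estimate bias in this trial, and the contradiction stands without it.

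**The case against.** The best defence is that the two sentences describe different people. The Discussion speaks of a subset, the physicians who direct nutrition and stand apart from the investigators, while section 2.2 speaks of clinicians generally and gives a bedside reason. A treating team can include a nutrition physician, so section 2.3.3 does not rule this out. The product is also formulated to stay fairly thin during tube administration. This stands as a possibility, and it is why the article cannot be said to prove which version is right. It does not remove the conflict: section 2.2 itself says the supplemented feed can be told apart in routine practice, and independence from the investigators is not blinding.

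A second objection is that the article already admits performance bias and an open-label design, so correcting one sentence changes no actual bias. That is true. What changes is what readers are told was done about it.

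Some stronger readings are tempting but unsupported:

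- A reader might infer that the trial relied on physician blinding alone. It did not. Blinding comes first among several mitigations, alongside independence from the investigators, the shared feeding protocol, and blinded assessment and analysis. The formula-based target also limits discretion over the target rate.
- A reader might infer that tube flushes reveal the arm because control patients have none. The article describes pectin-related flushes and is silent on flushing in usual care.
- Site stratification should not be counted as a protection here, since it does nothing about knowledge of the arm within a site.

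**Conclusion.** The point holds as an internal contradiction about who was blinded, on a matter that bears directly on the primary outcome. The methods and the described regimen fit section 2.2 better, but that is an inference; a blinded prescriber who goes undescribed cannot be excluded. One of the two passages needs correcting in either case.

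The size and direction of any resulting bias are unknown. A reader might take the sensitivity figures as evidence that the type I error is inflated or power lost by a stated amount. The documents do not support that: the holding difference is assumed, its range includes zero, and its cost depends on whether an hour is valued at the full target rate or at mean delivery. This is a correction that should be made. It does not overturn the design.

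**What to change.** State one version in section 2.2 and use it throughout.

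- **If section 2.2 is right:** delete only the closing clause of the Discussion sentence, the one claiming that the physicians were blinded. Keep their independence from the investigators, the shared CCCNTG feeding protocol, and the blinded assessment and analysis. Add that the clinicians making feeding decisions knew the arm, so performance bias on the primary outcome remains.
- **If a blinded nutrition prescriber was used:** correct section 2.2 to name that role and say how pectin orders and boluses were concealed from it. In section 2.3.3, name the same role and the feeding decisions it makes.

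The cost is a text correction, with no change to patients, data, analysis or sample size. The downside is that the trial may give up a claimed safeguard, and a limitation it already admits becomes stronger.
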